## 2. Study methods

### 2.1 Trial design

This is an international, multicentre, randomised parallel group control trial. Infants will be randomized in a variable block randomization scheduled, stratified by centre and gestational age, to one of two arms: the investigational arm consisting of oropharyngeal surfactant and standard-of-care (CPAP) and the control arm consisting of standard-of-care (CPAP) only.

Infants born less than 29 weeks' gestational age will be included if the treating physician plans to offer intensive care. Infants will be excluded if infants have major congenital anomalies and if the treating physician does not plan to offer intensive care. Written informed consent will be obtained before delivery.

**Figure 1: Study Schema**

[figure not shown]

### 2.2 Framework for analysis

|         |                                           |              |
|---------|-------------------------------------------|--------------|
| UCD CRC | SAP for the POPART trial                  |              |
| UCD CRC | Template: Statistical Analysis Plan (SAP) | Version: 1.0 |
|         |                                           | Page 8 of 19 |

Analysis of efficacy endpoints will be carried-out following the Intention-To-Treat (ITT) principle. A Per Protocol analysis will also be carried out on the primary endpoint for sensitivity analysis. For all statistical analysis, a p-value < 0.05 will be considered statistically significant.

Interim analysis of the primary endpoint and the important secondary endpoint, death before hospital discharge, will be performed by an external data safety monitoring board. This will be performed once half the planned sample (126 participants) have completed the trial.

For the primary analysis of the primary endpoint, a superiority hypothesis test (two-sided, two-proportion Z test) will be carried out to investigate whether the rate of endotracheal intubation differs between intervention and standard-of-care. In this analysis, infants intubated for signs of respiratory failure will be considered to have met the primary endpoint.

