#### 14.5.2 Secondary efficacy endpoints

Each categorical secondary endpoint will be analysed with the following approach.

- Descriptive statistics will be calculated to compare the rate of occurrence of the endpoint across treatment groups (frequency, percentage). Ratios of relative risk will be presented with 95% confidence intervals.
- A superiority hypothesis test (two-sided, two-proportion Z test) will be carried out to investigate whether the rate of occurrence of the endpoint differs between intervention and standard-of-care.

For the important secondary endpoint of death before hospital discharge, regression analysis will be employed to determine sensitivity of the estimated intervention effect to potentially relevant covariates; including centre, gestational age, birth weight, gender, mode of delivery (vaginal versus caesarean birth) and antenatal corticosteroid treatment.

Each quantitative secondary endpoint (e.g. duration of mechanical ventilation, duration of hospitalisation), will be analysed using the following approach.

- Descriptive statistics will be calculated to compare the endpoint across treatment groups (mean, median, standard deviation, IQR, min, max). The difference in means (or medians where relevant) between treatment groups will be presented with a 95% confidence interval.
- A superiority hypothesis test (two-sided independent sample t-test) will be carried out to test for a difference in means between control and intervention. Alternatively, if t-test assumptions are not valid, a Mann-Whitney U test will be carried out to test for a difference in the endpoint between control and intervention.

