## 1.2 Objectives

The primary objective is to investigate the efficacy of prophylactic oropharyngeal surfactant for reducing the rate of endotracheal intubation, compared to no intervention in infants at risk of RDS.

The secondary objective is to investigate the efficacy of prophylactic oropharyngeal surfactant compared to no intervention for preventing some possible complications in premature infants at risk of RDS. We will also record a number of variables relating to prematurity, from enrolment into the trial until discharge home from hospital.

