### 3. Statistical principles

#### 3.1 Confidence intervals and *P* values

The type I error rate for interim analysis will be set to 0.001 in accordance with the Haybittle-Peto stopping boundary. For final analysis, the type I error rate will be set at 0.05. Confidence intervals will be reported at a 95% confidence level.

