#### Secondary endpoints analysis

Mortality is an intercurrent event that could potentially occur before observation of many of the secondary endpoints in this trial in addition to the primary endpoint. Most secondary outcomes will involve evaluation of the intervention effect to be expected in infants while alive. Analysis of secondary endpoints will be performed on the intention-to-treat set of all randomised infants. The exceptions to this are

- Number of attempts taken to successfully intubate in the delivery room – will only be assessed for those who need to be intubated in the delivery room (intubation in the delivery room is indicated by variable **dr\_infant\_intub.factor**)
- Rectal temperature on admission to NICU as well as NICU intubation will only be evaluated for infants who are admitted to NICU alive (identified by derived variable **nicu\_admission**)

|         |                                           |              |               |
|---------|-------------------------------------------|--------------|---------------|
| UCD CRC | SAP for the POPART trial                  |              |               |
| UCD CRC | Template: Statistical Analysis Plan (SAP) | Version: 1.0 |               |
|         |                                           |              | Page 13 of 19 |

- Bronchopulmonary dysplasia (BPD) – supplemental O2 at 28 days of life - will only be evaluated for infants who are alive at 28 days of life (infants alive at 28 days to be determined by the variable **bpd\_d28.factor** )
- Chronic lung disease of prematurity (CLD), the need for supplemental O2 at 36 weeks corrected gestational age (CGA) determined by physiological oxygen reduction test - will only be evaluated for infants who are alive at 36 weeks CGA (determined by the variable **cld\_36wks.factor** )
- Duration of hospitalisation will be summarized and analyzed both for infants who survive to hospital discharge and for the whole sample. A similar approach will be used for days of mechanical ventilation and days of respiratory support.

Each categorical secondary endpoint will be analysed using the same approach as the main analysis of the primary endpoint.

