For the time-to-event endpoint death before hospital discharge, Kaplan-Meier curves will be constructed to visualize the pattern of mortality over the study period, with median survival time reported with 95% confidence intervals. Cox proportional hazards regression will be used to quantify the hazard ratio for those treated with oropharyngeal surfactant vs standard-of-care. A Cox proportional hazards regression model will also be fitted to determine sensitivity of the estimated intervention effect to potentially relevant covariates; including centre, gestational age, birth weight, gender, mode of delivery (vaginal versus caesarean birth) and antenatal corticosteroid treatment.

Each numeric secondary endpoint (e.g. duration of mechanical ventilation, duration of hospitalisation), will be analysed using the following approach.

- Descriptive statistics will be calculated to compare the endpoint across treatment groups. This will include the frequency of missing data per treatment arm, minimum and maximum values, mean and standard deviation for symmetrically distributed variables and median and interquartile range for asymmetrically distributed variables. The difference in means (or medians where relevant) between treatment groups will be presented with a 95% confidence interval. Confidence intervals for the difference in means will use a Normal approximation while confidence intervals for the difference in medians will be calculated by bootstrap resampling.
- A superiority hypothesis test (two-sided independent sample t-test) will be carried out to test for a difference in means between control and intervention. Alternatively, if t-test assumptions are not valid, a Mann-Whitney U test will be carried out to test for a difference in the the endpoint between control and intervention.

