### 5.1.3 Subgroup analyses

Subgroups of interest include infants of different gestational age strata (e.g. less than 26 weeks, and 26-28 weeks gestation at birth), and infants from different participating centres. Subgroup analysis of the primary endpoint and the important secondary outcome of death before hospital discharge will be carried out for these subgroups by:

- For each subgroup, the primary endpoint will be summarized per treatment arm by frequency and percentage, including the frequency of missing data. Relative risk of the primary endpoint will be estimated along with 95% confidence intervals for each subgroup, as per the main analysis of the primary endpoint.
- Log binomial regression of the primary endpoint will be conducted to evaluate interaction effects for treatment type and centre (if centre sample size permits), and for treatment type and gestational age, with the acknowledgement that this analysis is not likely to have sufficient statistical power.

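### About 30 secondary endpoints are each tested at p<0.05 under a rule covering all analyses, with no hierarchy, multiplicity adjustment or exploratory label

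*Combined protocol and SAP*

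**What the plan says.** The decision rule appears in the same words in SAP section 2.2 and protocol section 14.5: "For all statistical analysis, a p-value < 0.05 will be considered statistically significant". SAP section 3.1 adds "For final analysis, the type I error rate will be set at 0.05". The stricter 0.001 level applies only to the interim look.

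The secondary analyses are framed as tests of efficacy:

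- SAP section 1.2: "The secondary objective is to investigate the efficacy of prophylactic oropharyngeal surfactant compared to no intervention for preventing some possible complications".
- Protocol section 14.5.2, for each categorical endpoint: "A superiority hypothesis test (two-sided, two-proportion Z test) will be carried out to investigate whether the rate of occurrence of the endpoint differs" between the arms.
- SAP section 5.1.1: "Each categorical secondary endpoint will be analysed using the same approach as the main analysis of the primary endpoint".
- SAP section 5.1.1, for each numeric endpoint: "A superiority hypothesis test (two-sided independent sample t-test) will be carried out to test for a difference in means between control and intervention". A Mann-Whitney test is the fallback.
- SAP section 5.1.1: "Duration of hospitalisation will be summarized and analyzed both for infants who survive to hospital discharge and for the whole sample". Days of ventilation and days of respiratory support are treated similarly.
- SAP section 5.1.3: "Log binomial regression of the primary endpoint will be conducted to evaluate interaction effects for treatment type and centre", if centre sizes allow, and likewise for gestational age. The SAP concedes that these analyses probably lack power.

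Neither document contains a testing order, an alpha split or an adjustment for the number of tests. Death before discharge is called important, but no order or share of alpha follows from that at the final analysis. The word exploratory occurs only in the combined heading of protocol section 10.3 and is attached to no endpoint. SAP section 6 reports no departure from the protocol.

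**The concern.** The primary test is single and clearly named, so it is not at issue. The difficulty is that the plan does more than stay silent about secondary endpoints. It states that one threshold governs everything, and it prescribes a superiority test for each endpoint under an efficacy objective. Followed as written, the report would describe p=0.03 for chronic lung disease or intraventricular haemorrhage in the same terms as the primary result.

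The trial is open-label and its sample size was set for the primary endpoint alone. With this many tests, a reader of the final report would have no pre-specified basis for telling a chance secondary finding from a confirmed one, whether the primary result is null or positive.

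**Working it through.** **The plan's own figure.** The documents state no error rate across the secondary tests. The only figure to reproduce is the primary sample size in protocol section 14.2: 46% against 28%, two-sided 5%, 80% power.

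n per arm = [1.960 × √(2 × 0.37 × 0.63) + 0.8416 × √(0.46 × 0.54 + 0.28 × 0.72)]² / 0.18² = 111.75, rounded up to 112. Two arms give 224, as stated. Allowing for 10% loss, 224 / 0.9 = 248.9, so 249; the plan recruits 250. This calculation covers one test at 0.05, and nothing below alters it.

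**Counting the tests.** SAP section 1.3 has 27 top-level secondary endpoints. Splitting surfactant use into its three sub-items adds 2, and splitting intraventricular haemorrhage into any and severe adds 1: 27 + 2 + 1 = 30. Of these, 23 are binary and 7 numeric (intubation attempts, rectal temperature, two dose counts, ventilation days, respiratory support days, duration of hospitalisation). Number of doses including total dose is counted once. The second analysis of three durations would make 33. I use 30.

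**Expected false positives** if there is no true effect on any secondary endpoint: 30 × 0.05 = 1.5, whatever the correlation.

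**Chance of at least one, independent tests.**

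- Either direction: 1 − 0.95^30 = 0.785.
- Favouring surfactant only (0.025 per test): 1 − 0.975^30 = 0.532.

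**Chance of at least one, correlated tests.** Assume a common correlation ρ between the 30 test statistics: Z = √ρ × U + √(1−ρ) × E, with U shared and E specific to each test. Conditional on U the tests are independent, so

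P(either direction) = 1 − ∫ [Φ((1.96 − √ρ u)/√(1−ρ)) − Φ((−1.96 − √ρ u)/√(1−ρ))]^30 φ(u) du.

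For false benefit only, drop the second Φ term. Numerical integration and a simulation of 200,000 draws per setting agree to within 0.2 percentage points:

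| ρ (assumed) | At least one, either direction | At least one false benefit |
|---|---|---|
| 0 | 79% | 53% |
| 0.1 | 77% | 46% |
| 0.3 | 66% | 35% |
| 0.5 | 51% | 25% |
| 0.7 | 34% | 17% |

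For comparison, one test gives 5% in either direction and 2.5% in favour of surfactant.

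**Cross-check at infant level.** A simulated trial with 125 per arm, 24 binary and 6 continuous endpoints, a shared latent severity and assumed event rates of 3% to 85% gave 79% falling to 58% in either direction as the latent correlation rose from 0 to 0.7. For false benefit it gave 54% falling to 31%. Latent correlation is not on the same scale as ρ above.

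**The case against.** The strongest reply is that the plan already has two tiers in practice. The sample size, the estimand and the sensitivity analyses all centre on the primary endpoint; protocol section 10.3 mentions exploratory endpoints in its heading; estimates with 95% confidence intervals are already required for the secondaries; and the SAP admits that the interaction analyses are weak. Most readers would treat secondary results as supportive without being told.

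Part of this stands. The primary inference is sound and the estimates are already planned. But a generic heading classifies no endpoint, and it sits beside an explicit rule pointing the other way. Low power concerns missed effects; it does nothing about false positives.

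The size of the problem can also be overstated, and four stronger readings should be resisted:

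- A reader might infer that a false efficacy finding is more likely than not. For a false benefit of surfactant that holds only near independence (53%); it is already 46% at correlation 0.1. The figures of 51% to 79% include false harms and require no true effect on any secondary endpoint.
- Even in either direction, the chance falls below one half at high correlation. Several endpoints overlap by construction, such as BPD, CLD and survival without each.
- A reader might set these figures against a stated familywise 5%. The documents set 0.05 for the final analysis but define no rate across the secondaries.
- Counts well above 30 need inference. The Cox model for death is described as quantifying a hazard ratio, and the SAP's interaction bullet names only the primary endpoint.

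Whether a chance result would become the headline is speculation about reporting. The documents show only that the rule would permit it to be called significant.

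**Conclusion.** The gap is real and limited to the secondary, subgroup and interaction analyses. Under the stated rule, 30 secondary tests would yield 1.5 false positives on average if none of the endpoints is truly affected. That average does not depend on correlation.

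The chance of at least one does: from 79% down to 34% in either direction over correlations 0 to 0.7, and from 53% down to 25% for a false benefit over correlations 0 to 0.5. These ranges assume a common correlation, which simplifies a list mixing closely related lung outcomes with unrelated ones, and the documents give no values to narrow them. Even 25% is ten times the 2.5% for a single test in that direction.

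This warrants a short clarification. It does not threaten the primary analysis.

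**What to change.** In the SAP, before database lock, replace the threshold sentence in section 2.2 with:

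*The only confirmatory test at the final analysis is the two-sided Z test of the primary endpoint in the full analysis set at 0.05. Secondary endpoint, subgroup and interaction analyses are exploratory: they are reported as estimates with unadjusted 95% confidence intervals, any p-values are nominal, and no claim of efficacy or statistical significance will be based on them.*

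Add that the DSMB's p<0.001 interim guideline for death and all safety review are unchanged, so that no harm signal is suppressed. Record the change in SAP section 6. Rewriting the protocol is unnecessary: version 2.1 notes that close-out had begun at some sites.

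If the sponsor wants a formal final claim on death, make it the single second step of a fixed sequence, tested only after a significant primary result and with one named test. The name matters because the SAP treats death as time-to-event with a Cox model, while its general rule for categorical endpoints would also give it a Z test.

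The cost is wording only: no new data, infants or analyses. The sponsor gives up calling an individual secondary result statistically significant.

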### 2.3 Statistical interim analyses and stopping guidance

Efficacy interim analysis of the primary outcome and the important secondary outcome of death before hospital discharge will be performed on half of the planned sample (126 subjects) by a DSMB. The Haybittle-Peto boundary will be used as a stopping rule. Therefore, the DSMB may recommend terminating the study early for large and statistically significant differences ( $p < 0.001$ ) between groups in the primary outcome or in the important secondary outcome of death before hospital discharge; or for unanticipated concerns regarding the safety of enrolled infants.

The type I error rate for interim analysis will be set to 0.001 in accordance with the Haybittle-Peto stopping boundary. For final analysis, the type I error rate will be set at 0.05. Confidence intervals will be reported at a 95% confidence level.

### 2.4 Timing of final analysis

Final analysis will be carried out when all subjects reach the last study visit, data entry and validation is completed and the database is locked.

### 2.5 Timing of outcome assessments

Infants will be randomised at delivery. Infants randomised to oropharyngeal surfactant will receive a dose of surfactant. Infants randomised to the control group will not have anything injected into their oropharynx and will be stabilised on CPAP in the DR as per routine practice.

The primary endpoint is the incidence of endotracheal intubation for respiratory failure within 120 hours of birth. Other secondary outcomes have predefined outcome measures and will be recorded on the individual CRF during the course of hospitalisation.

|         |                                           |              |
|---------|-------------------------------------------|--------------|
| UCD CRC | SAP for the POPART trial                  |              |
| UCD CRC | Template: Statistical Analysis Plan (SAP) | Version: 1.0 |
|         |                                           | Page 9 of 19 |

### 3. Statistical principles

#### 3.1 Confidence intervals and *P* values

The type I error rate for interim analysis will be set to 0.001 in accordance with the Haybittle-Peto stopping boundary. For final analysis, the type I error rate will be set at 0.05. Confidence intervals will be reported at a 95% confidence level.

#### 3.2 Analysis populations

##### 3.2.1 Full analysis set (FAS)

The Full Analysis Set (FAS) will include all trial subjects enrolled into the trial and randomised. The evaluation is carried out strictly in accordance with the allocation by randomization according to the intention-to-treat principle (ITT).

##### 3.2.2 Per-protocol (PP)

The per-protocol (PP) population includes subjects in the Full Analysis Set, excluding those with relevant protocol deviations which could affect the evaluation of primary endpoint. The Per Protocol set will exclude:

- Infants in the intervention arm who did not receive study treatment
- Infants with incomplete data on the primary endpoint

##### 3.2.3 Safety population

Patients in the intervention arm who received prophylactic surfactant and all patients in the control arm (for comparison)

|         |                                           |               |
|---------|-------------------------------------------|---------------|
| UCD CRC | SAP for the POPART trial                  |               |
| UCD CRC | Template: Statistical Analysis Plan (SAP) | Version: 1.0  |
|         |                                           | Page 10 of 19 |

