### 14.3 Analysis sets

This table defines the sets of subjects whose data are to be included in the statistical analyses.

|                                                     |                                                                                                                                                                                                                                                                                                                                                                        |
|-----------------------------------------------------|------------------------------------------------------------------------------------------------------------------------------------------------------------------------------------------------------------------------------------------------------------------------------------------------------------------------------------------------------------------------|
| Full Analysis Set
(Intention-To-Treat principle) | All randomized patients                                                                                                                                                                                                                                                                                                                                                |
| Per Protocol Set                                    | Patients in the Full Analysis Set, excluding those with relevant protocol deviations which could affect the evaluation of primary endpoint. The Per Protocol set will exclude: 
 
• Infants in the intervention arm who did not receive study treatment
 
• Infants with incomplete data on the primary endpoint
 
 |
| Safety Set                                          | Patients in the intervention arm who received prophylactic surfactant and all patients in the control arm (for comparison)                                                                                                                                                                                                                                             |

Efficacy analysis will be carried out following the Intention-To-Treat (ITT) principle. Per protocol analysis of the primary endpoint will also be carried out for sensitivity analysis. Safety data will be analysed using the safety set.

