##### **Adverse events**

The number of adverse events (i.e. all events occurring, worsening or becoming serious after the randomisation), and the number and percentage of infants reported as having at least one emergent adverse event, will be reported by system organ class and preferred term, for each treatment group.

The same description will be performed for serious adverse events (SAE), severe AE, AE treatment related and AE leading to IMP withdrawal.

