## 5. Analysis

### 5.1 Analysis methods

#### 5.1.1 Primary analysis

The primary estimand in this trial is the difference in the rates of endotracheal intubation for respiratory failure while alive within 120 hours of birth in future infants treated with prophylactic oropharyngeal surfactant compared to infants treated with the standard of care (no intervention). The primary analysis will be done on the full analysis set according to the intention-to-treat principle. For infants who died within 120 hours of randomization, the primary endpoint will be documented for the time period in which they were alive. Infants who were intubated without (or prior to) meeting the definition of respiratory failure defined in the protocol will be included, and will be considered to have met the primary endpoint in the main analysis.

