#### 5.4 Safety evaluation

Adverse events will be summarized for each site and for the whole sample, including:

- Total number of adverse events
  - Number and percentage of adverse events that were serious (SAES)
  - Number and percentage of adverse events that were mild, moderate and severe
  - Number and percentage of treatment-related adverse events
  - Number and percentage of adverse events that were resolved without sequelae, resolved with sequelae, ongoing, or resulted in death.
- Number of deaths (all causes) per treatment arm
- Number of deaths resulting from adverse events per treatment arm
- Number and percentage of subjects experiencing
  - Any adverse event
  - Any serious adverse event
  - Mild, moderate and severe adverse events
  - Treatment-related adverse events

Further, any non-serious adverse event occurring with a greater than 5% frequency in either treatment arm, will be described by treatment arm, including:

- System organ class
- Event term
- Number of subjects per treatment arm affected by the event
- Total number of events of this type that occurred per treatment arm

For all serious adverse events (SAEs), the above information will be reported as well as:

- Number of these SAEs causally related to treatment, per treatment arm
- Number of these SAEs with fatal outcome, per treatment arm
- Number of treatment-related SAEs of this type with fatal outcome

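### The safety and per-protocol sets drop undosed infants from the surfactant arm only, which may bias both comparisons in either direction; SAP 5.4 also omits the arm from its overall adverse event counts

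*Combined protocol and SAP*

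**What the plan says.** **Safety set.** SAP 3.2.3 takes "Patients in the intervention arm who received prophylactic surfactant and all patients in the control arm (for comparison". The definition matches protocol 14.3, which adds that "Safety data will be analysed using the safety set". Protocol 14.6 left the definition to be settled in the SAP, and the SAP repeats it unchanged.

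**Per-protocol set.** SAP 3.2.2 starts from the full analysis set, "excluding those with relevant protocol deviations which could affect the evaluation of primary endpoint". It then names two exclusions: "Infants in the intervention arm who did not receive study treatment" and "Infants with incomplete data on the primary endpoint". Only the first of these is tied to an arm.

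**Where the sets are used.** For the main result, SAP 5.1.1 states that "The primary analysis will be done on the full analysis set according to the intention-to-treat principle". The per-protocol set serves one sensitivity analysis of the primary endpoint (SAP 2.2 and 5.1.2). The section of SAP 5.1.1 on secondary endpoints puts them on all randomised infants, with listed exceptions.

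**Adverse event tables.** SAP 5.4 opens with "Adverse events will be summarized for each site and for the whole sample, including". Protocol 14.6 says that adverse event counts, and infants with at least one event, "will be reported by system organ class and preferred term, for each treatment group", and applies the same to serious, severe and treatment-related events. SAP section 6 declares no departure from the protocol's main statistical features.

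**The concern.** The envelope is opened just before delivery (protocol 11.3.6), and the dose is due within five minutes of birth (protocol 11.1). Whether an infant is dosed is therefore decided after allocation, by staff who know the arm. Removing undosed infants from one arm conditions on a post-randomisation event. The controls who would also have gone undosed cannot be identified, so they stay, and the two groups no longer have the balance that randomisation gave them.

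Two uses are exposed. The per-protocol analysis is meant to show whether the effect is sensitive to deviations, but a shift caused by selection would look the same. The safety tables, read with protocol 14.3, would omit a surfactant-arm infant who died undosed while counting every control death. The safety set also treats a control given oropharyngeal surfactant in error as an untreated control.

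Overall adverse event totals that do not name the arm cannot show a difference between arms, which is what protocol 14.6 asks them to do.

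**Working it through.** **The plan's own figure.** The 46% control rate comes from protocol 14.2 (46% v 28%, two-sided 5%, 80% power). With the pooled-variance formula, n per arm = [1.96·√(2·0.37·0.63) + 0.842·√(0.46·0.54 + 0.28·0.72)]² / 0.18² = 111.8, so 112 per arm and 224 in total. Then 224/0.90 = 249, against 250 stated. The sample size reproduces and this point does not affect it.

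**Effect of the one-arm exclusion.** Let p be the event rate in both arms (no true effect), f the share of the surfactant arm not dosed, and q the event rate in undosed infants. The documents give neither f nor q, so both are assumptions shown over a range.

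Expected rate in dosed infants = (p − f·q)/(1 − f), compared with p in controls.

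Primary endpoint, p = 46%:

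| f | q = 80% | q = 46% | q = 20% |
|---|---|---|---|
| 2% | 45.3%, −0.7 points | 46.0%, 0 | 46.5%, +0.5 points |
| 5% | 44.2%, −1.8 points | 46.0%, 0 | 47.4%, +1.4 points |
| 10% | 42.2%, −3.8 points | 46.0%, 0 | 48.9%, +2.9 points |

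Example: (0.46 − 0.05·0.80)/0.95 = 0.42/0.95 = 0.442. At f = 5% the relative risk runs from 0.96 (q = 80%) to 1.03 (q = 20%).

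**False-positive rate in favour of surfactant.** Take 125 randomised per arm and a two-sided 5% pooled Z test. The rate is 2.5% when undosed infants stay in their arm. With them dropped it becomes:

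- f = 5%: 4.7% at q = 80%, 1.5% at q = 20%
- f = 10%: 8.4% at q = 80%, 0.8% at q = 20%

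**Safety illustration.** With an assumed event rate of 10% in both arms and f = 5%:

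- q = 30%: (0.10 − 0.015)/0.95 = 8.9%, a difference of −1.1 points (relative risk 0.89)
- q = 0%: 0.10/0.95 = 10.5%, a difference of +0.5 points

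**Adverse event tables side by side.**

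| Item | Protocol 14.6 | SAP 5.4 |
|---|---|---|
| Total events; serious, severe, related | By treatment group | By site and whole sample; arm not named |
| Infants with any event | By treatment group | Arm not named |
| Deaths, all-cause and from adverse events | Not itemised | By arm |
| Non-serious events above 5% in either arm | By treatment group | By arm |
| Serious events by type | By treatment group | By arm |

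The mismatch is in the overall counts, not in every table.

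**The case against.** The strongest case on the other side has four parts.

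- **Controls can leave the per-protocol set.** The general deviation rule and the incomplete-data rule apply to both arms, and the general rule could remove a control given surfactant. This stands. Only the safety set keeps every control.
- **The direction is not documented.** A reader might infer that both sets tilt towards surfactant because the sickest infants are the ones missed. This is plausible. Infants are intubated in the delivery room for persistent apnoea or bradycardia, so one intubated before dosing would be both undosed and a primary event. Yet nothing says who goes undosed, and the protocol intends dosing ideally before cord clamping and within five minutes for every infant. If non-dosing is unrelated to prognosis the bias is zero, and if undosed infants are healthier it reverses. This objection stands.
- **Most harm outcomes are already compared as randomised.** Death, pneumothorax, pulmonary haemorrhage, intraventricular haemorrhage and the delivery-room events are secondary endpoints. Death also has Kaplan-Meier and Cox analyses. Protocol 13.3 routes several of these conditions to the secondary outcomes instead of to adverse event reports. This stands and limits the impact.
- **The site and whole-sample wording does not say that arms are pooled, and protocol 14.6 still applies.** This stands only in part. Within one list the SAP names the arm for deaths and leaves it out for the other overall counts, so a programmer following the SAP could omit it.

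None of this answers the core point: undosed infants are removed from one arm only, after randomisation.

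**Conclusion.** The point holds as a possible bias of unknown direction in two secondary uses of the data, together with a mismatch between SAP 5.4 and protocol 14.6. Under no true effect, with 46% intubated and 5% undosed, the per-protocol difference lies between -1.8 and +1.4 points as the intubation rate in undosed infants goes from 80% to 20%. With 2% undosed the range is -0.7 to +0.5 points. These sizes rest wholly on assumed non-dosing rates and prognosis.

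The documents do not support saying that both sets keep every control, or that both comparisons are biased in favour of surfactant. Nor do they support saying that deaths are compared only in the dosed set. The primary analysis is untouched, and death and the other secondary endpoints are analysed in all randomised infants, with exceptions that do not depend on dosing. The mismatch in the overall adverse event counts needs no assumption. The changes are worth making, but the trial's main conclusion does not depend on them.

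**What to change.** 1. In SAP 5.4, report every item, including deaths and serious adverse events, by randomised arm in all randomised infants. Keep the dosed-only set of SAP 3.2.3 as a supplement. This removes the selection and restores agreement with protocol 14.6.
2. State how a control given oropharyngeal surfactant is handled in the safety and per-protocol sets, and list the relevant deviations for both arms.
3. Tabulate undosed surfactant-arm infants with number, reason and outcome. SAP 4.5 already has the reasons recorded.
4. Label the per-protocol result as open to selection after randomisation.
5. Optionally, add a complier-average effect (the intention-to-treat risk difference divided by the difference between arms in the proportion dosed). State its assumption that allocation acts only through dosing, which is doubtful when unmasked staff decide on intubation. It need not replace the per-protocol analysis.

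The cost is SAP wording and minor reprogramming, with no new data collection. The drawback is that undosed infants slightly dilute surfactant-arm event rates. If the undosed share were 5%, an excess caused by dosing would appear at 0.95 of its size, and the supplementary dosed-only table shows the undiluted rate.
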